**Methods:**

We developed a protocol for a web-based adaptive intervention trial to investigate the effectiveness of goal recommendation (task difficulty) based on reinforcement learning. The web application (named Apptivate) creates workout routines with 3 different difficulty levels, changing the total workout duration as well as rest times between exercises. Physical activity professionals validated the routine design, ensuring that workouts match recommended guidelines for healthy adults. An initial pilot was conducted, aiming for 800 university students to test the web application for 1 week, to provide initial data to calibrate the algorithm as well as overall feedback for the web application. For the main study, a total of 500 university students will be recruited to participate for 40 days during early 2026. Participants will be divided into 3 groups: user choice (no recommendation), user choice with automated recommendations (contextual bandits), and automated plans without choice.

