## Methods

### Apptivate

For this project, the experiment will be conducted using the web application “Apptivate” [45], extending its initial functionally to incorporate CB algorithms connected to a routine difficulty assignment. Apptivate creates workout routines with 3 different difficulty levels, changing the total workout duration as well as rest times between exercises. PA professionals validated the routine design, ensuring that workouts match recommended guidelines for healthy adults. The overall design allows users to conduct exercises without equipment following the in-app instructions, covering different muscle groups as well as providing both warm-up and stretching exercises.

Apptivate adopts the IBC model for PA [26] as a framework for tailoring workout difficulty recommendations (ie, goals). By leveraging the IBC model, the app ensures that its recommendations address not only dynamic changes in behavior over time but also the psychological factors that influence behavior change. In particular, we capture data on the psychological constructs defined in the IBC model, which are later used as contexts for the algorithm learning process. Participants that take part in the main study will be assigned to 1 of 3 conditions:

Choice-driven: Users select their desired workout difficulty level from a predefined menu. This approach provides users with a sense of autonomy and control over their exercise routine. Choice-driven tailoring leaves the selection of the intervention to the user, allowing individuals to reveal their preferences in a participatory process [33].Data-recommended: The CB algorithm determines optimal workout difficulty (based on user data and the IBC model) and provides a recommendation to the user, but the user retains the option to choose an alternative. This design allows us to investigate the interplay between user autonomy and the effectiveness of data-driven recommendations [27].Data-driven: The CB algorithm automatically recommends workouts based on user data, including contextual features based on the IBC model, without any opportunity to opt into a different difficulty level. This method leverages a machine learning approach to personalize workout plans and potentially optimize user performance (measured as goal completion).

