### Study Design

This study poses two main hypotheses: (1) goal personalization with CBs decreases the intention-behavior gap for some users, and (2) the effectiveness of such goal personalization on behavior is mediated through individual choice. To explore these hypotheses, participants will be randomly assigned to 1 of 3 groups: choice-driven, data-recommended, or data-driven.

The target population are university students (both undergraduate and graduate) from different institutions, allowing for differences in region, language, and time zone of the participants. Randomization will be stratified by baseline demographic factors, including household composition, income, age, and gender, to ensure a representative sample within each institution. The inclusion criteria require participants to be physically healthy adults (aged older than 18 years), with access to a smartphone compatible with the mobile web application. Exclusion criteria include significant physical disabilities or medical conditions limiting exercise, based on the Physical Activity Readiness Questionnaire [46], as well as individuals actively participating in competitive sports. The participant assignment procedure will use block randomization to reduce bias and ensure even group distribution, with allocations concealed and blinded from both participants and researchers through a secure system managed by the data specialist team. Data will be stored at a secure server at the University of Concepcion, with backups of the database each hour. A deidentified version of the data and dictionary can be made available upon request.

Since there is no prior evidence regarding effect size for this study, sample size was determined using 1000 simulations, following existing guidelines [47]. Sample sizes were estimated considering the particularities of adaptive experiment design. Simulations based on the relevant populations were conducted using the epsilon-greedy algorithm. Based on simulated data, a sample size of 500 participants during 10 rounds is sufficient to evaluate differences between intervention arms and conduct statistical inference, particularly regarding demographic and behavioral characteristics between participants. The authors are currently working on a publication describing the simulations and associated power analysis, which will become available in late 2025.

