To train the reinforcement learning algorithm for the study, initial data are required for which a pilot stage was designed. In this stage, 800 participants will be recruited at one university in order to provide 1 week of activity using the app (two 3-day rounds with a rest day in between). In order to determine the sample size for the pilot, standard power calculation was assumed with a uniform distribution over 3 arms (standard randomized controlled trial). With 665 observations, the pilot is sufficient to detect differences between users. The data from round 1 will be used to estimate the optimal arm for round 2, which will be used for calibration. Participants complete a comprehensive baseline survey eliciting the IBC model as well as several other relevant characteristics (eg, time and risk preferences; see Multimedia Appendix 1) and then are assigned randomly between the 3 difficulty levels for the first round. After completion, participants are compensated for their time. Individuals can opt out from the study at any time.

During the main part of the study, 500 participants will be recruited from multiple sites expecting to participate in a medium-term challenge, completing 10 rounds, equivalent to 39 consecutive days using the app (including rest days). As noted earlier, this provides 5000 unique examples for the algorithm to determine optimal policy over time. Users will be allocated to each arm based on their baseline survey and the trained algorithm during the pilot stage. Regardless of their initial difficulty assignment, each participant will be randomly allocated with equal probability between (1) choice-driven, (2) data-recommended, and (3) data-driven arms. Participants will be compensated for their time, and there will be additional prizes using a lottery mechanism that favors (in probability) those users completing more consecutive workout routines over the course of the study. In both the pilot and main experiment, participants will stay engaged via direct email, push notifications, and social media campaigns.

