### Statistical Analysis

Statistical analysis will focus on comparing goal completion rates, engagement metrics, and user satisfaction across the 3 intervention groups. To address missing data, a multiple imputation approach will be applied to ensure robustness in outcome estimates. The primary analysis will estimate the conditional average treatment effect for each intervention arm, with subgroup analyses to identify variations by demographics, baseline fitness, and psychological factors. Mixed-effects models will account for repeated measures and clustering within participants, while sensitivity analyses will assess the robustness of the findings under varying assumptions.

During the pilot phase, multiple CB algorithms will be evaluated based on metrics such as regret minimization (difference between actual and optimal rewards) and balance between exploration and exploitation. The main experiment will focus on estimating the conditional average treatment effect and analyzing differences in goal completion rates and engagement metrics. Subgroup analyses will explore how demographic characteristics (eg, age and gender), motivational factors, and baseline fitness levels influence responsiveness. Metrics such as cumulative reward, prediction accuracy, and contextual feature importance will be analyzed to evaluate the algorithm’s ability to personalize recommendations effectively.

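### The protocol says allocation is blinded from participants, but the three arms differ visibly to the user, so only concealment before assignment is possible

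*Protocol article*

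**What the plan says.** In the Study Design section, the sentence on block randomization ends "with allocations concealed and blinded from both participants and researchers through a secure system managed by the data specialist team". The same section states that "each participant will be randomly allocated with equal probability between (1) choice-driven, (2) data-recommended, and (3) data-driven arms".

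The Apptivate section defines the arms by the user's interaction with the app:

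- Choice-driven: "Users select their desired workout difficulty level from a predefined menu".
- Data-recommended: the algorithm "provides a recommendation to the user, but the user retains the option to choose an alternative".
- Data-driven: the algorithm sets the level "without any opportunity to opt into a different difficulty level".

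The Methods paragraph of the abstract gives the same three-way split: "user choice (no recommendation), user choice with automated recommendations (contextual bandits), and automated plans without choice".

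The Statistical Analysis section plans on "comparing goal completion rates, engagement metrics, and user satisfaction across the 3 intervention groups". The limitations under Anticipated Findings cover dropout and generalizability but not blinding.

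**The concern.** The Study Design sentence names two properties, concealment and blinding, and applies both to participants. Concealment concerns what is known before assignment and is achievable here. Blinding concerns what is known afterwards. When the treatment consists of having or not having a choice, and of seeing or not seeing a recommendation, the participant experiences the assigned condition directly.

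What is at stake is the protection from bias that the trial can claim. A reader who takes the sentence at face value would credit the arm comparisons with participant blinding, including the comparison of user satisfaction, which depends on the participant's own perception. The abstract and the Conclusions both promise robust causal inference on the role of choice, so the blinding status behind that inference should be stated correctly.

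**Working it through.** No arithmetic applies, because no figure in the plan depends on the blinding statement. The check sets the statement beside the arm definitions.

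**Step 1. What each arm shows the user (Apptivate section, Methods paragraph of the abstract).**

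| Arm | Recommendation shown | User can choose the level |
|---|---|---|
| Choice-driven | No | Yes |
| Data-recommended | Yes | Yes |
| Data-driven | Level assigned by the algorithm | No |

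**Step 2. Pairwise contrasts.** Three arms give three contrasts.

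- Choice-driven against data-recommended: they differ in whether a recommendation appears.
- Data-recommended against data-driven: they differ in whether the level can be changed.
- Choice-driven against data-driven: they differ in whether the user or the algorithm sets the level.

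No two arms look the same to the user.

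**Step 3. Is the difference masked?** The article describes no sham menu, dummy recommendation or other device that would make the interfaces alike.

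**Step 4. Could it be masked without losing the question?** Of the choice-driven arm, the Apptivate section says: "This approach provides users with a sense of autonomy and control over their exercise routine". The user has to perceive the condition for that mechanism to work. The third research question in the Introduction asks how autonomy changes the effectiveness of recommendations. Hiding the condition would remove the contrast being studied.

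**Step 5. What remains possible.** The upcoming allocation can be concealed through the system run by the data specialist team. Researchers and analysts can be masked, and the Data Collection section helps here because the app tracks goal completion, activity time and engagement. Nothing in the article contradicts blinding of researchers.

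**Step 6. Which outcomes are exposed.** Satisfaction depends on the participant's perception of a condition they know. Goal completion and engagement are tracked by the app, so there is less room for reporting bias. The article does not say whether completion is marked by the user or verified, and it does not describe how satisfaction is measured. The size of any bias therefore cannot be derived from it.

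**The case against.** The strongest reply is that the sentence is about the assignment procedure. On that reading, neither participants nor researchers know or can influence the allocation when it is made, and the two terms are a loose way of saying one thing. The article never calls the trial double-blind and does not rest its inference on blinding. Participants may also be unaware of the other arms or of the hypotheses; the consent material is not available, so this cannot be settled. These points make the intent more innocent, but the wording still applies blinding expressly to participants. Unawareness of the alternatives is a weaker property than blinding to allocation and, if it is what is meant, should be stated as such.

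A second reply stands in full. A reader might infer that disappointment at being denied a choice contaminates the estimate of the algorithm's effect. The documents do not support treating that reaction as a bias. Autonomy is an object of study in the third objective, the third research question and the second hypothesis. Moreover, the comparison of data-recommended with choice-driven involves no denial of choice, since both arms keep it.

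Two further inferences go beyond the text. One is that students in different arms will compare app versions; the article offers no evidence of this. The other is that participant contact differs by arm; the Study Design section describes emails, notifications and campaigns without any such difference. Nor is there a case for demanding that the main outcome rest on app data, since goal completion is already tracked by the app and the Results section makes success rates the main comparison.

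The condensed format of a journal article does not answer the point, which concerns a statement that was made, not a detail left out.

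**Conclusion.** The point holds as a correction to a stated property of the design. Participants can be kept from knowing the upcoming allocation, but they cannot be blinded to the condition they receive. An open-label interface is unavoidable given the research question and is not criticised here; the error lies in claiming otherwise.

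The statement covers all 500 planned participants, but that is the reach of the claim and not a measure of bias. No figure, sample size or main analysis changes. The practical consequence is likely to be largest for user satisfaction and smaller for app-tracked completion.

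The conclusion assumes that the arms are delivered as the Apptivate section describes them, with no undisclosed masking of the interface. It does not extend to researchers or analysts, whose masking is feasible and is not contradicted.

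**What to change.** Reword the Study Design sentence to state three things separately:

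1. Allocation is concealed until assignment.
2. Participants are not blinded to their condition. If it is true, add that they are not told of the other arms or of the hypotheses.
3. Researchers and analysts are masked through coded arm labels until the primary analysis is locked.

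Report user-satisfaction contrasts as open-label comparisons, and add the lack of participant blinding to the limitations under Anticipated Findings. The changes should be in place before results are reported; the Results section anticipates publication in late 2026.

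The cost is a few sentences and coded labels in the analysis file. The downside is that the stated blinding becomes less favourable. Randomization, data collection and the main analysis stay as they are.

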### Data Collection

Data collection in this study spans multiple dimensions, capturing individual characteristics, app usage patterns, and most importantly, user performance. This multifaceted approach allows us to provide insights on the potential heterogeneous impact of tailored goal-setting interventions.

Baseline survey: Participants will complete an online survey to gather demographic information (eg, age, gender, and socioeconomic status), fitness history (eg, frequency and type of PA), and constructs from the IBC model, such as perceived behavioral control, motivation types (autonomous and controlled), and self-regulatory capacities.Fitness app data: The app will track participant engagement and outcomes, including goal completion rates, total time spent on physical activities, and engagement metrics (eg, frequency of app interactions).Algorithm data: The CB algorithm embedded in the app will collect data on contextual features (eg, user preferences, past performance, and fitness level) and reward functions to predict optimal goals and adapt recommendations over time.

### Statistical Analysis

Statistical analysis will focus on comparing goal completion rates, engagement metrics, and user satisfaction across the 3 intervention groups. To address missing data, a multiple imputation approach will be applied to ensure robustness in outcome estimates. The primary analysis will estimate the conditional average treatment effect for each intervention arm, with subgroup analyses to identify variations by demographics, baseline fitness, and psychological factors. Mixed-effects models will account for repeated measures and clustering within participants, while sensitivity analyses will assess the robustness of the findings under varying assumptions.

During the pilot phase, multiple CB algorithms will be evaluated based on metrics such as regret minimization (difference between actual and optimal rewards) and balance between exploration and exploitation. The main experiment will focus on estimating the conditional average treatment effect and analyzing differences in goal completion rates and engagement metrics. Subgroup analyses will explore how demographic characteristics (eg, age and gender), motivational factors, and baseline fitness levels influence responsiveness. Metrics such as cumulative reward, prediction accuracy, and contextual feature importance will be analyzed to evaluate the algorithm’s ability to personalize recommendations effectively.

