## Abstract

**Background:**

The incidence of chronic diseases associated with physical inactivity is on the rise, being one of the leading risk-increasing factors for early death rates throughout the world. Often, physical activity interventions fail to deliver sustained adherence over time due to limiting tailoring to individual baseline characteristics, leaving out contextual changes over time. One solution for this issue may be the use of adaptive interventions relying on contextual multiarmed bandits, a type of reinforcement learning algorithm, that can use baseline and contextual individual data to personalize aspects of the intervention, such as developing personalized workout plans.

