**Objective:**

The main objectives of this study are (1) to determine the effectiveness of contextual bandits for automated goal setting in the context of a web-based physical activity intervention, (2) to understand the role of user characteristics impacting ideal workout schedules based on adherence to predetermined goals, and (3) to explore the influence of user autonomy on recommendation effectiveness.

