## Discussion

### Anticipated Findings

This study introduces a novel approach to promoting sustained PA through a mobile app, leveraging CB learning for personalized goal difficulty recommendations, under an IBC framework. By combining this theory-informed machine learning approach with different levels of user autonomy, the intervention addresses critical gaps in existing mHealth literature, particularly the role of autonomy and motivation on personalized goal setting. We expect to find heterogeneity in both (1) individual behavioral responses to personalized goals, and (2) autonomy preferences for choice versus automation. Such heterogeneity should align with the IBC model and reflect the particular hurdles of motivation versus goal difficulty.

Findings from this field experiment will contribute to the growing field of adaptive digital health technologies, offering practical insights for scaling effective interventions for sustained health behavior. Ultimately, this research has the potential to inform public health strategies by providing evidence on the interplay between user autonomy and data-driven recommendations, fostering more engaging and effective health behavior change digital tools.

There are limitations to this study. First, participant dropout may introduce bias if attrition is nonrandom, reducing overall statistical power. Our sample size considers a maximum 20% dropout rate, to maintain statistical validity. Second, findings may not generalize to populations of different ages or health statuses or to those without smartphone access and from other cultural contexts beyond those included in the study. In an effort to provide better external validity, we aim to implement this study in countries with different languages and cultural backgrounds.

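### Multiple imputation of outcomes, applied without exception, would credit completed rounds to participants who stopped using the app and shrink any arm difference that acts through quitting

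*Protocol article*

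**What the plan says.** The Statistical Analysis section first names the outcomes: "Statistical analysis will focus on comparing goal completion rates, engagement metrics, and user satisfaction across the 3 intervention groups". The next sentence gives the only rule for missing data: "To address missing data, a multiple imputation approach will be applied to ensure robustness in outcome estimates". It makes no exception for people who stop using the app. Sensitivity analyses under varying assumptions are promised, but the assumptions are not named.

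The Data Collection section says how the main outcomes arise: "The app will track participant engagement and outcomes, including goal completion rates, total time spent on physical activities, and engagement metrics".

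Dropout appears in the limitations under Anticipated Findings, where "participant dropout may introduce bias if attrition is nonrandom, reducing overall statistical power". The next sentence adds: "Our sample size considers a maximum 20% dropout rate, to maintain statistical validity". No other source of outcome loss is named.

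The target is adherence. The abstract's Background gives the problem: "Often, physical activity interventions fail to deliver sustained adherence over time". One of the three objectives is "to understand the role of user characteristics impacting ideal workout schedules based on adherence to predetermined goals".

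**The concern.** A missing value is one that exists but was not seen. For an outcome logged by the app, a scheduled round with no logged completion is normally not of that kind: the in-app goal was not met, and the value is zero. The same holds for frequency of app use after a person has left. Imputing such rounds answers another question, namely what quitters would have done had they continued.

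This matters most for the autonomy question. To justify the choice arm, the Introduction cites a meta-analysis in which choice-based interventions improved adherence and lowered dropout. Lower dropout is thus one of the routes by which the protocol itself expects choice to work. If one arm loses more users, for example the arm without choice, imputation fills that arm's empty rounds at about the rate of similar people who stayed, or at the rate of the quitters' own earlier rounds. The part of the arm difference that came from quitting then shrinks or disappears. Completion is also inflated in every arm, even when quitting is equal.

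**Working it through.** **Inputs from the protocol article.** Study Design: 500 participants, 10 rounds, equal allocation to three arms. Anticipated Findings: dropout of at most 20%.

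**The plan's own figure.** 500 × 10 = 5000 participant-rounds, which matches the 5000 examples stated in Study Design.

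**How many rounds are exposed.** At the 20% ceiling, 100 people quit. If they lose 25% to 100% of their rounds, that is 5000 × 0.20 × 0.25 = 250 to 5000 × 0.20 × 1.00 = 1000 rounds, or 5% to 20% of the total.

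**Assumptions for the illustration (not in the article).** Completion while active is p = 0.65 in both arms. Quitting is d = 0.20 in data-driven and 0.10 in choice-driven. Everyone who quits does so after round s. Quitters complete at the same rate as stayers while active.

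**Formulas.** With unlogged rounds counted as not completed, an arm's rate is p × [1 − d × (10 − s)/10]. Under missing-at-random imputation it is about p.

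| Quit after round s | Choice-driven | Data-driven | Difference, unlogged = not completed | Difference, imputed |
|---|---|---|---|---|
| 0 | 0.65 × 0.90 = 0.585 | 0.65 × 0.80 = 0.520 | −6.5 points | about 0 |
| 3 | 0.65 × 0.93 = 0.6045 | 0.65 × 0.86 = 0.559 | −4.6 points | about 0 |
| 5 | 0.65 × 0.95 = 0.6175 | 0.65 × 0.90 = 0.585 | −3.3 points | about 0 |

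With 30% versus 10% quitting, the lost difference is 0.65 × 0.20 × 0.5 = 6.5 points (s = 5) to 0.65 × 0.20 × 1 = 13 points (s = 0).

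**Inflation without any arm difference.** With 20% quitting in every arm and half of the quitters' rounds lost, p = 0.50 to 0.80 gives true rates of 0.45 to 0.72, against 0.50 to 0.80 after imputation.

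**Simulation check.** The set-up was 1000 replicates, 167 people per arm, 10 rounds, person-level completion probabilities with mean 0.70, and quitting of 10% versus 30% at uniform times and unrelated to completion. Empty rounds were filled with the expected value given each person's earlier rounds. Counting them as not completed gives 0.665 versus 0.594, a difference of 7.1 points. The formula gives 0.70 × (1 − 0.10 × 0.5) = 0.665 and 0.70 × (1 − 0.30 × 0.5) = 0.595. Imputation gives 0.70 versus 0.70.

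**If quitters differ from stayers.** Let q be the quitters' completion rate while active, and let imputation recover it from their earlier rounds. Imputation then adds q × d × (10 − s)/10 to each arm, so the lost difference is q × (difference in d) × (10 − s)/10. It equals the figures above when q = p, is smaller when q is below p, and is zero only if quitters had completed nothing.

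**The case against.** The strongest reply is that the article never says an unlogged round is coded as missing. A rule for missing data does not reach a value that is known to be zero. The Contextual Bandits Algorithm section points that way: users respond positively or negatively, and the response is a reward that trains the algorithm, so a negative response can be an observed value. Imputation also has other natural targets, such as baseline survey items used in the conditional effects and user satisfaction. Coding of withdrawal is often left to a fuller plan, nonrandom attrition is acknowledged, and multiple imputation need not assume missing at random.

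Much of this stands. A reader might infer that the plan has declared post-dropout rounds missing, or has committed to missing at random. It states neither. The first is the natural reading of two sections taken together, and the second is the usual default. A reader might also infer that imputation turns quitters into successes, or always returns a zero difference. It gives them a predicted rate, and the near-zero result needs equal completion while active.

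The objection does not remove the point. The imputation sentence is aimed at outcome estimates, follows directly on the naming of goal completion and engagement, and has no exception. Dropout is the one loss the article names, and it is discussed as bias and lost power, not as an outcome. The bandit description does not settle how rounds after dropout are coded. The unnamed sensitivity analyses leave the main rule as it is.

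**Conclusion.** The concern holds as a fault in a stated rule. As written, it would naturally be applied to rounds after a participant stops using the app, and there it does not fit an app-logged adherence outcome. With standard imputation, completion is inflated in every arm whenever some people quit who would have been predicted to complete some rounds. Any arm difference that acts through quitting is attenuated.

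The direction follows from the method; the size rests on assumed rates. In the illustration, a difference of 3.3 to 6.5 points (20% versus 10% quitting) would be largely lost, and less if quitters were already completing fewer rounds. The article gives no quitting rate by arm and no completion rate. It therefore does not support a claim that the trial's result will be biased by a given amount, or that the autonomy effect will be erased. If a fuller plan already codes non-use as not completed, the harm disappears, but this text does not say so.

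**What to change.** Replace the single imputation sentence with a rule by type of data:

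- **Primary analysis:** keep all randomised participants and all 10 scheduled rounds in the denominator. Count any round without a logged completion, including rounds after dropout, as not completed.
- **Multiple imputation:** restrict it to survey items, user satisfaction and rounds lost to documented technical failure.
- **Reporting:** give the number quitting and the round of quitting, by arm.
- **Sensitivity analyses:** name them. Include imputation of post-dropout rounds (with a delta-adjusted, not-at-random version) and a while-active analysis.

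The change costs wording and makes the main analysis simpler. The downside is that reported completion rates become lower. It should be settled before the main study starts.
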